### **7.2.5 Safety Analysis**

#### **7.2.5.1 Adverse Reactions**

All adverse reactions reported during trial period shall be charted and calculated for its incidence rate.

Ratio and frequency of subjects exhibiting adverse reactions in each group will be calculated and the adverse reaction incidence rates will be compared using the chi-square test or the Fisher's exact test. Same goes for drug reaction, serious adverse reaction, and adverse reaction causing the trial stoppage as incidence rate and frequency are suggested by administration group.

Occurring adverse reactions shall be summarized by administration group, body organ, and preferred term.

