based on such study results. It reviewed the appropriate dosage through a two-phase clinical trial conducted at Gangnam Severance Hospital and Seoul Asan Medical Center. And it conducted a comparative clinical trial against the standard drug of diclofenac sodium which is known to have outstanding pain relieving effect among anti-inflammatory pain relievers through Gangnam Severance Hospital and 6 other institutions to complete the verification of safety and effectiveness.

Pelubipirofen was authorized for sale by KFDA in April of 2007 as effective drug for osteoarthritis based on domestic two-phase and three-phase clinical trial results as well as clinical trial results from Japan.

In 2009, clinical trials for addition of effect on backache were conducted through Soonchunhyang University Hospital and 9 other institutions to complete the verification of safety and effectiveness in the comparative clinical trial against aceclofenac tablets for KFDA approval in January 2011.

In 2010, clinical trials comparing the effectiveness and safety against that of celecoxib capsule in rheumatoid arthritis patients were conducted through Seoul National University Hospital and 13 other institutions to receive additional approval from KFDA as of July 2012. Pelubi tablet(Pelubipirofen 30mg) as a result has secured various clinical effectiveness for controlling pain caused from osteoarthritis, backache, and rheumatoid arthritis.

Daewon Pharmaceutical Co., Ltd. Also developed the Pelubi CR tablet(Pelubipirofen 45mg) which is taken twice per day to sustain effective drug concentration level for 12 hours equivalent to a slow release version of quick release drug Pelubi tablet(Pelubipirofen 30mg) which is taken 3 times per day in order to improve convenience for patients medicated with pain reliever for chronic pain. And it conducted a comparative clinical trial against Pelubi tablet on chronic backache patients in 2014. It was observed in the results of these clinical trials that Pelubi CR tablet(Pelubipirofen 45mg) exhibited similar pain relief effect compared to the traditional quick release tablet and the incidence rates of adverse event for the test group was 17.72%(14/79 people, 17 cases) while it was 17.50%(14/80 people, 20 cases) for the control group which was statistically insignificant. The company received approval for sale

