from KFDA as Pelubi CR tablet being effective in terms of pain relief for osteoarthritis, backache, and rheumathritis in April 2015 based on clinical trial results above.

Daewon Pharmaceutical Co., Ltd. planned this clinical trial to conduct a phase 4 clinical trial within the authorized area for Pelubi CR tablet(Pelubiprofen 45mg) to secure safety data and to confirm its clinical effectiveness. This clinical trial utilized aceclofenac tablet as control drug to confirm the safety and effectiveness of Pelubi CR tablet(Pelubiprofen 45mg) in patients with osteoarthritis of the knee.

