#### **7.2.2 General Statistical Principles**

Verification of all statistical significance shall be performed by a two-tail test

with significance level( $\alpha$ ) of 5%. However, noninferiority will be verified using the confidence interval.

Main analysis of data regarding effectiveness from subjects of this clinical trial shall be performed through PPS followed by additional analysis of FAS by principle.

Analysis of data regarding safety shall be performed through the safety analysis set.

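### The only between-arm inference named for adverse reaction rates is a chi-square or Fisher test, which does not show how large an excess over aceclofenac remains possible (minor)

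*Protocol*

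**What the plan says.** Section 2.2 of the Protocol makes comparison of safety a secondary purpose, and the overall purpose in section 2 also mentions safety. Section 1.1 says that the trial "utilized aceclofenac tablet as control drug to confirm the safety and effectiveness of Pelubi CR tablet".

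For the analysis, section 7.2.5.1 first gives description: "Ratio and frequency of subjects exhibiting adverse reactions in each group will be calculated". It then names a test: "adverse reaction incidence rates will be compared using the chi-square test or the Fisher's exact test". Drug reactions, serious reactions and reactions that stop the trial are to be treated in the same way. The section ends with a tabulation: "Occurring adverse reactions shall be summarized by administration group, body organ, and preferred term". Sections 7.2.5.2 and 7.2.5.3 add laboratory, physical examination and vital-sign analyses.

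Section 7.2.2 supplies the level: "Verification of all statistical significance shall be performed by a two-tail test", at 5%. It then makes an exception: "However, noninferiority will be verified using the confidence interval". Section 7.2.4.1 applies that exception to the VAS endpoint, where an upper confidence limit is set against 15 mm. The protocol names no interval, margin or power for adverse reactions.

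**The concern.** A difference test can signal harm when the difference is large. When it is not significant, it does not show how much harm is still compatible with the data, and that is what a reader needs in order to compare safety with an active control. The protocol handles this correctly for pain, with a confidence limit, but names only a p-value for adverse reactions.

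The sample size in section 3.2.2 rests on the VAS margin alone, so nothing ensures that the safety test has useful power. At stake is how the result will be read. A non-significant p-value is a likely outcome even with a clinically relevant excess, and the planned inference would not show the reader how much excess remains possible.

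**Working it through.** **1. The plan's own sample size (section 3.2.2).** Inputs: SD 24.86 mm, margin 15 mm, one-sided α 0.025, power 0.975, no true difference.

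n = 2 × 24.86² × (1.960 + 1.960)² / 15² = 84.4, rounded up to 85 per group. With 10% loss, 85 / 0.90 = 94.4, rounded up to 95. Both figures reproduce. They concern pain only.

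**2. Inputs for the safety test.**
- Subjects per arm: at most 95. The safety set in section 7.2.1 is everyone randomised and dosed at least once, so the 10% loss is not deducted.
- Level: two-sided 5% (section 7.2.2).
- Control rate: not given for aceclofenac in knee osteoarthritis, so it is assumed. The rates in the protocol come from pelubiprofen trials. They are 17.50% and 17.72% (14/80 and 14/79, earlier backache trial, section 1.1), 12.66% and 13.75% (drug reactions in that trial, Appendix 11.1.1, 4.2), and 24.9% (pooled trials, Appendix 11.1.1, 4.1). The range used is 10% to 24.9%, where 10% is an assumed low end.
- Excess: 10 percentage points. This is illustrative, as the protocol states no safety difference of interest.

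**3. Miss rate at 17.5% against 27.5%, normal approximation.** The mean rate is 0.225.

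z = [0.10 × √95 − 1.960 × √(2 × 0.225 × 0.775)] / √(0.175 × 0.825 + 0.275 × 0.725)
= (0.975 − 1.157) / 0.586 = −0.31

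Power is Φ(−0.31) = 0.378, so the miss rate is 62.2%.

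**4. Exact enumeration.** This sums the binomial probabilities of all outcome pairs with 95 per arm.

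| Control rate | With 10-point excess | Missed, uncorrected chi-square | Missed, Fisher |
|---|---|---|---|
| 10% | 20% | 51% | 58% |
| 13.75% | 23.75% | 57% | 64% |
| 17.5% | 27.5% | 62% | 68% |
| 24.9% | 34.9% | 67% | 73% |

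Other excesses from a 17.5% control rate, by uncorrected chi-square: a true 22.5% is missed in 86% of trials and a true 32.5% in 33%.

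**5. What an interval would show.** With equal observed rates of 17.5% and 95 per arm, the half-width of the 95% interval for the difference is

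1.96 × √(2 × 0.175 × 0.825 / 95) = 0.108.

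The interval is about −10.8 to +10.8 points. A p-value near 1 would therefore still leave an excess of almost 11 points compatible with the data.

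**The case against.** The strongest reply is that the protocol draws no wrong inference. Non-inferiority is claimed for pain relief only, and safety is a secondary comparison without a hypothesis of its own. A reader might infer that the sponsor intends to take non-significance as proof of comparable safety, since section 1.1 describes the adverse event rate in the earlier CR trial against that of the "control group which was statistically insignificant". The protocol does not support that reading. The sentence reports the history of a trial with nearly identical rates (17.72% and 17.50%), and no rule of this kind is set for the present trial.

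A reader might also infer that the whole safety comparison rests on a p-value. It does not. Rates per group, summaries by organ and term, and laboratory, vital-sign and physical examination analyses are planned, and the risk difference can be worked out from the tabulated counts.

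It is fair, too, that low power for adverse events is normal in a trial sized on efficacy, that the sample size is right for its stated purpose, and that an interval could be added in the statistical analysis plan. The missing interval is therefore not an error.

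What remains is narrower. The protocol does name an inference for adverse reaction rates, and the one it names is not the most informative for a comparison with an active control.

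**Conclusion.** The point holds as a minor improvement and not as an error in the plan. The chi-square or Fisher test is the only between-arm inference named for adverse reaction rates, and at this sample size a non-significant result says little about the excess that remains possible. A 10-point excess would be missed in about 51–67% of trials by the uncorrected chi-square test and 58–73% by Fisher's test. Equal observed rates near 17.5% would leave about ±11 points.

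These figures rest on 95 treated subjects per arm, on assumed control rates of 10% to 24.9% and on an excess chosen for illustration. No single figure, such as the 62% at a 17.5% control rate, should be quoted without its base rate and its test. The conclusion does not depend on the exact rate: over the whole range the test misses such an excess at least half the time.

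**What to change.** In section 7.2.5.1, make the between-arm risk difference (test minus control) with its two-sided 95% confidence interval, for example by Newcombe's method, the main comparison. Apply it to the categories that the section already lists: any adverse reaction, drug reaction, serious reaction, and reaction causing stoppage. Keep the chi-square or Fisher p-value as descriptive. Add one sentence saying that any statement of comparable safety is to rest on the upper confidence limit and not on p > 0.05.

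The cost is one short paragraph and one extra column in the safety tables, with no new data or subjects. The change adds no power, and the report will show openly how wide the uncertainty about safety is.

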#### **7.2.5.2 Clinical Laboratory Test**

Suggest descriptive statistics for results observed in clinical laboratory tests before treatment(Screening) and after conclusion of study drug administration. Also, perform the paired t-test or Wilcoxon signed rank test to analyze whether

there is difference in change between the groups after conclusion of study drug administration compared to prior to treatment(Screening).

Also, suggest the frequency and ratio of subjects who were normal/clinically insignificant abnormal before treatment(Screening) that changed to clinically significant abnormal patients after conclusion of study drug administration.

#### **7.2.5.3 Physical Examination and Vital Signs Examination Results**

As for physical examination, compare the results of physical examination before treatment(Screening) and after conclusion of study drug administration and summarize the results into frequency and percentage in order to determine the change in normal/abnormal.

As for vital signs, suggest the descriptive statistics of results measured prior to treatment(Screening) and after conclusion of study drug administration. Also, perform the paired t-test or Wilcoxon signed rank test to analyze whether there is difference in change between the groups after conclusion of study drug administration compared to prior to treatment(Screening).

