## Clinical Trial Schedule

|                                                              | Washout Period  | Administration Period |         |         |
|--------------------------------------------------------------|-----------------------------|-----------------------|---------|---------|
| Visit                                                        | Visit 1                     | Visit 2               | Visit 3 | Visit 4 |
| Day                                                          | Within 14 days before       | Day 1                 | Day 14  | Day 28  |
| Visit Window                                                 |                             |                       | ±3 day  | ±3 day  |
| Written consent form                                         | X                           |                       |         |         |
| Demographic data                                             | X                           |                       |         |         |
| Medical/Medication history                                   | X                           | X                     |         |         |
| Physical examination                                         | X                           | X                     | X       | X       |
| Vital signs / Weight                                         | X                           | X                     | X       | X       |
| ECG                                              | X                           |                       |         | X       |
| Laboratory Tests                                 | X               |                       |         | X       |
| X-ray examination                                | X                           |                       |         |         |
| ACR based test                                               | X                           |                       |         |         |
| Pregnancy test                                   | X                           |                       |         | X       |
| Assessment through inclusion/exclusion criteria              | X                           | X                     |         |         |
| Stoppage of pain reliever administration                     | X                           |                       |         |         |

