### **3. OVERALL DESIGN AND PLAN**

#### **3.1 Design**

This clinical trial was designed as a multicenter, randomized, double-blinded, parallel, active-controlled, phase IV clinical trial.

Once the subject gives written consent to participate in the clinical trial, subjects who have been medicated with non-steroid anti-inflammatory pain reliever including narcotic analgesic, osteoarthritis supplements and treated with physical therapy and oriental therapy(Acupuncture, cupping, moxibustion) within 2 weeks prior to administration of clinical trial must undergo a washout period by stopping the administration and application of such treatments for 3~14 days prior to administration of investigational product. Screening period including the washout period cannot exceed 2 weeks.

Subjects who are not restricted in terms of prohibited medication and therapy prior to screening visit can skip the washout period if they meet the subject qualification criteria and be administered with investigational product.

Subjects who are qualified as the result of qualification examination results according to the selection criteria after completing the washout period are randomly assigned at the ratio of 1:1 to control group or test group. Randomly assigned subjects are medicated with study drug or control drug for 28 days and they are evaluated in terms of effectiveness and safety by visiting the testing institution on day 14 and 28 after medication.  
frequency

[figure not shown]

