## **4.2 Procedure by Visit**

### **4.2.1 Visit 1(Screening and Washout Period, 14 Days Prior to Trial)**

Subjects selected for participation in this study shall be evaluated according to following sequence after listening to description of the study.

- 1) Describe trial procedure to subject and receive written consent form from subject prior to participation.
- 2) Assign screening number to subject in sequence of consent.
- 3) Survey and record demographic data and medical/medication history(Past and current history including surgeries).
- 4) Measure vital signs and weight and conduct physical examination.
- 5) Measure weight.
- 6) Conduct laboratory tests(Hematologic test, blood chemistry test, urine test, blood coagulation test).
- 7) Conduct pregnancy test for female subjects of childbearing age.
- 8) Perform ECG.
- 9) Conduct x-ray examination.
- 10) Evaluate according to ACR diagnosis criteria.
- 11) Evaluate according to inclusion/exclusion criteria.
- 12) Stop administration if subject is being regularly medicated with pain reliever and such and train on the washout period over 3~14 DAYS.

- 13) Evaluate 100mm Pain VAS.
- 14) Prescribe rescue drug.
- 15) Train on rescue drug log writing and distribute rescue drug log.
- 16) Schedule next visit.

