#### **4.2.2 Visit 2(Random Assignment and Administration of Investigational product, Day 1)**

This visit takes place after washout period(3~14 days) for subjects administered pain relievers and such and the evaluations for this visit are as below.

- 1) Check for changes in medical/medication history compared to previous visit.
- 2) Check for washout period for pain reliever, etc.
- 3) Measure vital signs and weight and conduct physical examination.
- 4) Evaluate 100mm Pain VAS.
- 5) Combine all examination and evaluation results including clinical lab results up until this point and perform final evaluations whether qualified subjects according to inclusion/exclusion criteria have been selected.
- 6) Assign assignment number through random assignment.
- 7) Evaluate K-WOMAC.
- 8) Train on administration method and distribute investigational products.
- 9) Recover residual clinical trials from the subject and record residual quantity.
- 10) Distribute new rescue drug.
- 11) Train on rescue drug log writing and distribute new rescue drug log.
- 12) Schedule next visit.

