are co-administration with oral corticosteroid or anticoagulant, long term use of non-steroid anti-inflammatory pain reliever with alcohol consumption, old age, and weak physical state. Most of voluntary reports regarding fatal gastrointestinal reactions come from elderlies and physically weak people so administration of this drug for such patients should be cautious.

- (8)High blood pressure: Non-steroid anti-inflammatory pain relievers including this drug may cause high blood pressure or aggravate existing high blood pressure and such may result in increase in occurrence of cardiovascular failures. Patient administered thiazide diuretic or loop diuretic whom are medicated with non-steroid anti-inflammatory pain reliever may experience reduced reaction from such treatment. Non-steroid anti-inflammatory pain relievers including this drug must be administered with caution for high blood pressure patients. Blood pressure must be closely monitored during early stage of administration and throughout the administration period for this drug.
- (9)Congestive heart failure and edema: Fluid retention and edema were observed in some patients medicated with this drug and other non-steroid anti-inflammatory pain reliever. This drug should be administered with caution for patients with fluid retention or cardiac insufficiency.
- (10)Long term administration of non-steroid anti-inflammatory pain reliever may cause renal papillary necrosis or other renal damage. Also, special caution is required for cardiac insufficiency patients, renal function disorder patients, liver function disorder patients, patients administered with diuretic or ACE inhibitor, and elderlies since the role of prostaglandin is critical for maintaining RBF. Most patients should recover to state before treatment once administration is suspended.
- (11)Progressing renal disease: There are no controlled clinical trials regarding usage of this drug on patients with progressed renal disease. Therefore, administration of this drug is not recommended for patients with progressed renal disease. Renal function of the patient should be monitored closely if administration of this drug is necessary.

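### Vital signs and physical examination are compared with Screening, taken before analgesics are stopped, although post-washout pre-dose values exist at Visit 2; within-arm change can be attenuated

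*Protocol*

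**What the plan says.** Protocol section 7.2.5.3 fixes the comparison point for two safety domains. For vital signs: "As for vital signs, suggest the descriptive statistics of results measured prior to treatment(Screening) and after conclusion of study drug administration". For physical examination, the plan is to "compare the results of physical examination before treatment(Screening) and after conclusion of study drug administration" and tabulate the move between normal and abnormal. For the change in vital signs it says to "perform the paired t-test or Wilcoxon signed rank test to analyze whether there is difference in change between the groups".

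Screening is Visit 1. Section 3.1 says that subjects on NSAIDs and certain other treatments "must undergo a washout period by stopping the administration and application of such treatments" for 3 to 14 days before the first dose. Section 4.2.1 places the start of that washout within Visit 1: "Stop administration if subject is being regularly medicated with pain reliever and such and train on the washout period over 3~14 DAYS".

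Visit 2 is Day 1 and follows the washout. Section 4.2.2 lists this step: "Measure vital signs and weight and conduct physical examination". The row "Vital signs / Weight" in the Clinical Trial Schedule is marked at all four visits, as is physical examination, and section 4.1.2.3 also asks for vital signs at every visit.

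The precautions for the study drug in section 11.1.1 warn: "Non-steroid anti-inflammatory pain relievers including this drug may cause high blood pressure or aggravate existing high blood pressure". Section 11.1.2 carries the same warning for the comparator, and both sections mention fluid retention and oedema.

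**The concern.** A pre-treatment value should describe the subject without the drug under study or another of its class. For a subject who arrives on an NSAID, the Visit 1 value does not do that. If the earlier NSAID had raised blood pressure, the rise is already in the starting value, and the change to the end of treatment looks smaller than the change from the washed-out state. The Visit 2 value is nearer to what is wanted. It is already collected and goes unused.

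The trial has no placebo arm, so the within-arm change and the shift table are the main view in these summaries of each drug's absolute effect on blood pressure, a risk that the protocol itself names. Section 1.1 gives safety data on the study drug as a reason for the trial. The tests named in 7.2.5.3 are paired, within-subject tests, so they act on the affected quantity even though the sentence speaks of a difference between groups.

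**Working it through.** The protocol gives no figure on this point. Its sample size (85 evaluable and 95 enrolled per group) does not depend on the safety baseline.

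**1. Order of procedures** (sections 4.2.1 and 4.2.2)

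| | Visit 1 | Visit 2 |
|---|---|---|
| Vital signs and physical examination | step 4 | step 3 |
| Analgesics stopped | step 12 | already stopped; checked at step 2 |
| Randomisation | – | step 6 |
| Investigational product dispensed | – | step 8 |
| Used as pre-treatment value in 7.2.5.3 | yes | no |

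For a subject on an NSAID at entry, Visit 1 is before washout. Visit 2 is after washout and before dosing. Elsewhere the protocol starts from Visit 2: the pain entry threshold is applied there (section 5.1) and K-WOMAC is first measured there (Schedule). Section 7.2.5.2 also uses Screening for laboratory tests, but Screening is their only scheduled pre-dose measurement. That reason does not extend to vital signs or examination.

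**2. Within-arm change in blood pressure**

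Let D be the mean change from Visit 2 to the end of treatment, f the share of subjects on an NSAID at Visit 1, and b the part of that NSAID's effect that is present at Visit 1 and gone by Visit 2. The mean Visit 1 value then lies f × b above the mean Visit 2 value, so

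change from Screening = D − f × b.

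The documents give none of D, f or b. On assumed values:

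- Understatement f × b: 0.3 × 3 = 0.9 mmHg, up to 0.9 × 5 = 4.5 mmHg.
- f = 0.5 and b = D: for D = 3, 3 − 1.5 = 1.5 mmHg; for D = 5, 5 − 2.5 = 2.5 mmHg. Half remains.
- f = 0.5 and b = D/2: for D = 3, 3 − 0.75 = 2.25 mmHg; for D = 5, 5 − 1.25 = 3.75 mmHg. Three quarters remains.
- Limits: with f = 0 nothing is lost; with f = 1 and b = D the apparent change is zero.

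**3. Between-arm difference**

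Visits 1 and 2 both precede dosing, and the vital signs at each are taken before randomisation. In expectation, f × b is therefore the same in both arms and cancels. With a true change of 4 mmHg in one arm and 6 mmHg in the other, and b = 4: (6 − 4f) − (4 − 4f) = 2 mmHg for f = 0, 0.5 and 1.

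**4. Examination shifts**

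Take a subject with an abnormal sign at Visit 1 on a prior NSAID, normal at Visit 2 after washout, and abnormal again at the end of treatment. From Screening this counts as abnormal to abnormal, that is, no change. From Visit 2 it counts as normal to abnormal. The opposite error is also possible: a sign that first appears between Visit 1 and the first dose is counted from Screening as a shift on treatment.

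**The case against.** The strongest reply is that the stated safety objective in section 2.2 is a comparison of the two drugs, and the comparison survives. Step 3 confirms that a common pre-randomisation baseline leaves the between-arm difference unbiased in expectation. That stands in full.

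Three further points stand.

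- **Adverse-event route.** A reader might infer that the baseline hides the drugs' effect on blood pressure and oedema altogether. The documents do not support that. Section 4.1.2.4 sends significant examination findings after dosing that meet the adverse-event definition to the adverse-event record, and pre-dose symptoms and signs to current medical history. Section 8.1 counts changed examination results and clinically significant signs as adverse events, and section 7.2.5.1 compares incidence between arms.
- **Who is affected.** A reader might also infer that most subjects are compared on one NSAID with themselves on another. The share is not stated. Subjects without restricted treatment skip washout, and supplements, physical therapy or acupuncture can trigger it without any NSAID. The two-week look-back also takes in people who had already stopped.
- **Size.** The millimetre figures rest on assumed inputs. Any claim that up to 90% of the effect is lost merely restates the assumed f (4.5/5 = 0.9) and needs a prior NSAID as strong as the study drug. Washout may last only 3 days, so part of the earlier effect could persist at Visit 2, which makes b smaller.

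None of this gives a reason to prefer the Visit 1 value. If Screening was meant loosely to include Visit 2, the wording still needs correcting, because the protocol gives that name to Visit 1.

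**Conclusion.** The point holds in a limited form. Section 7.2.5.3 names a pre-washout value as the starting point when a post-washout, pre-dose value is already scheduled. For subjects on an NSAID at Screening, the within-arm change in blood pressure can be attenuated and examination shifts can be misclassified.

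The attenuation is about f × b and cannot be derived from the documents. The range of 0.9 to 4.5 mmHg holds only if f lies between 30% and 90% and b between 3 and 5 mmHg; it falls to zero if few subjects arrive on NSAIDs. No efficacy result and no sample-size figure is touched, and the randomised safety contrast is not biased in expectation. This is a worthwhile improvement at no cost to conduct, not a threat to the trial's conclusions. Confidence is high on what the protocol says and low on how large the effect would be.

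**What to change.** In section 7.2.5.3, replace Screening as the pre-treatment value with a sentence such as: *Baseline for vital signs and physical examination is the last value before the first dose of investigational product (Visit 2; the Screening value is used only if Visit 2 is missing). Screening values are listed descriptively.*

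Leave section 7.2.5.2 as it is, since laboratory tests have no Visit 2 measurement.

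The cost is one sentence and the matching change in the analysis programs. The data are already scheduled, and no visit, procedure or sample-size figure changes.

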#### **7.2.4.2 Secondary Effectiveness Analysis**

- 1) Change in 100mm Pain VAS on 14th day compared to baseline

Analysis through application of the same statistical method as the primary effectiveness evaluation variables.

- 2) Change in K-WOMAC scale on 14th and 28th day compared to baseline

Verify through the paired t-test for changes in total K-WOMAC score along with pain subscale, stiffness subscale, and physical function subscale on the 14th and the 28th days between test group and control group compared to the baseline.

Also, use the t-test to verify whether there is a difference between groups in terms of change on the 14th and the 28th day compared to baseline for each item.

- 3) Patient Global Assessment

Suggest the frequency and percentage of subjects evaluated as 'Very good(5)', 'Good(4)', 'No change(3)', 'Poor(2)', and 'Very poor(1)' on the 14th and the 28th day after investigational product administration and perform the chi-square test or the Fisher's exact test to see if there is a difference between groups.

If the overall assessment scores are 5 or 4, categorize as 'Response' and 'No response' if the scores are 3, 2, or 1 to suggest treatment response rates for each group. Perform the chi-square test or the Fisher's exact test to check for difference in treatment response rate between groups.

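### Laboratory and vital-sign change is to be compared between independent arms with paired tests, and no two-sample test is named

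*Protocol*

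**What the plan says.** Section 3.1 describes a "multicenter, randomized, double-blinded, parallel, active-controlled, phase IV clinical trial" with subjects "randomly assigned at the ratio of 1:1 to control group or test group". No matching of subjects across arms is described. Section 2.2 lists comparison of safety between the two drugs, including vital signs and laboratory tests, as a secondary purpose.

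The analysis sections then read as follows.

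- **Vital signs (7.2.5.3):** descriptive statistics, then "perform the paired t-test or Wilcoxon signed rank test to analyze whether there is difference in change between the groups".
- **Laboratory tests (7.2.5.2):** descriptive statistics, then the same choice of two tests as for vital signs, again aimed at a between-group difference in change from screening to the end of treatment. Counts of subjects moving to clinically significant abnormal values are also reported.
- **K-WOMAC (7.2.4.2):** "Verify through the paired t-test for changes in total K-WOMAC score along with pain subscale, stiffness subscale, and physical function subscale", worded as changes between the test and control groups. A second sentence follows: "use the t-test to verify whether there is a difference between groups in terms of change on the 14th and the 28th day".

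Section 7.2.2 sets a two-sided 5% level for significance tests. Section 7.2.4.1 analyses VAS change by covariance analysis with baseline VAS as covariate, and Section 7.2.4.2 applies the same method to Day 14 VAS.

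**The concern.** In the two safety sections the test and the question do not fit each other. The question is whether change differs between arms. The tests named work on pairs, and the only natural pairs here are the screening and end-of-treatment values of the same subject. Such a test asks whether the average change is zero. It carries no information on whether one drug moves a laboratory value or blood pressure more than the other.

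Since no other test of continuous change is named, an analyst who follows the text would produce one p-value per arm, or one for both arms pooled. Either could be reported as a comparison of the drugs. A common drift in both arms could look like a difference, and a real difference could go unseen.

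The first K-WOMAC sentence has the same wording fault, but the sentence after it supplies a between-group test.

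**Working it through.** **The plan's own figure.** The sample size is the only design calculation in the protocol. With SD 24.86 mm, margin 15 mm, one-sided alpha 0.025 and power 0.975 (Section 3.2.2):

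n = 2 × 24.86² × (1.96 + 1.96)² / 15² = 84.4, so 85 per group; 85 / 0.90 = 94.4, so 95 per group.

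Both stated figures reproduce, and nothing below changes them.

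**What each named test can answer**

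| Measure | Question in the protocol | Test named | Two-sample test also named? |
|---|---|---|---|
| Vital signs (7.2.5.3) | change between groups | paired t / signed rank | no |
| Laboratory (7.2.5.2) | change between groups | paired t / signed rank | no |
| K-WOMAC (7.2.4.2) | change between groups | paired t, then t-test between groups | yes |
| VAS (7.2.4.1, 7.2.4.2) | change between groups | ANCOVA on baseline | yes |

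**If the paired test is run in each arm and the two p-values are compared.** Let both arms have the same true change of d SD (SD of the change score), so there is no difference to find. The power p of a paired t-test with n = 95 at 5% two-sided comes from the noncentral t distribution with noncentrality d√95. The arms are independent, so the chance that exactly one is significant is 2p(1 − p).

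| Common shift d (assumed) | p | 2p(1 − p) |
|---|---|---|
| 0 | 0.050 | 10% |
| 0.1 | 0.161 | 27% |
| 0.2 | 0.488 | 50% |
| 0.3 | 0.825 | 29% |
| 0.4 | 0.971 | 6% |
| 0.5 | 0.998 | 0.4% |

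The expression 2p(1 − p) cannot exceed 0.50, and d = 0.2 lies almost exactly at that peak. With 85 per arm, the values at 0.1, 0.2 and 0.3 SD are 25%, 49% and 34%.

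**If one paired test is run on both arms pooled.** In a simulation with 85 per arm, 20,000 runs and normal change scores with SD 1:

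| True situation (assumed) | Paired test significant | Two-sample t-test significant |
|---|---|---|
| Equal arms, common shift 0.2 SD | 74% | 4.9% |
| Equal arms, common shift 0.3 SD | 97% | 4.6% |
| Equal arms, common shift 0.5 SD | 100% | 4.9% |
| Arms at +0.25 and −0.25 SD (true difference 0.5 SD) | 4% | 90% |

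Read as a comparison of arms, the pooled paired test responds to common drift and misses the opposite movement in 96% of runs. The two-sample test behaves as it should.

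**K-WOMAC precision.** For equal variances at baseline and follow-up with correlation rho, the variance of the ANCOVA estimate relative to the change-score estimate is (1 − rho²) / [2(1 − rho)] = (1 + rho)/2. At rho = 0.3, 0.5 and 0.7 this is 0.65, 0.75 and 0.85, a reduction of 35%, 25% and 15%. The protocol gives no rho, so these values are assumed.

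**The case against.** The best defence is that this is loose or translated wording. The authors probably meant a paired test within each arm and a separate test between arms, as they wrote for K-WOMAC. That is plausible, and it is why the remedy is small. But the second step is absent from both safety sections. Nor can this be treated as detail deferred to a SAP: the protocol names both the test and its purpose, and a SAP would have to depart from that text to be correct.

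It is also fair to say that these are supportive summaries. No decision rule depends on these p-values, and the protocol does not tell readers to compare one arm's p-value with the other's. That stands, and it limits the severity.

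Several stronger readings are tempting but are not supported.

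- **That the drugs are never compared on safety.** Section 7.2.5.1 compares adverse reaction incidence between arms by chi-square or Fisher's exact test, and Section 7.2.5.2 adds the shift counts. The gap is confined to continuous laboratory and vital-sign change.
- **That K-WOMAC is analysed without its baseline.** Baseline is measured at Visit 2 (Section 4.2.2) and subtracted to form the change (Section 7.1.2). The between-group t-test on that change is valid, and under randomisation it is unbiased. Section 7.2.3 also allows a covariate when a relevant baseline difference is seen. Prespecified adjustment would gain precision; its absence is not an error.
- **That half of all trials would mislead.** The 50% figure is the ceiling of 2p(1 − p), reached only near an assumed 0.2 SD shift.

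**Conclusion.** The point holds for Sections 7.2.5.2 and 7.2.5.3. The named tests cannot answer the stated between-group question, and no valid test of continuous laboratory or vital-sign change between arms is specified, although Section 2.2 makes that comparison a secondary purpose.

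The size depends on how the instruction is carried out and on shifts that the document does not give. If within-arm p-values are compared, false discordance runs from under 1% at 0.5 SD to a maximum of 50% at 0.2 SD. The calculation assumes normal change scores, equal true change in both arms and 95 per arm.

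For K-WOMAC, only the label of the first test needs correcting. Adding baseline as a covariate is optional and would lower variance by about 15% to 35% for assumed rho of 0.7 to 0.3 with equal variances.

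Severity is moderate and limited to secondary and safety analyses.

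**What to change.** - **Sections 7.2.5.2 and 7.2.5.3:** restrict the paired t-test and signed-rank test to change within each arm. For the comparison between arms, name a two-sample t-test or Wilcoxon rank-sum test on change from screening; ANCOVA with the screening value as covariate would also serve.
- **Section 7.2.4.2, K-WOMAC:** describe the paired t-test as within-arm, and leave the following t-test as the between-arm comparison.
- **Optional:** analyse K-WOMAC total and subscale change at Days 14 and 28 with the VAS model, with baseline K-WOMAC as a prespecified covariate.

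The cost is a wording change in the protocol, carried into the SAP. It needs no new data, visits or subjects.
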